### Hypotheses

#### Primary hypothesis

Participants in the extended Internet intervention condition will display significantly improved drinking outcomes at twelve months compared to participants in the minimal Internet intervention condition.

Secondary Hypotheses:**Secondary Hypothesis 1**: Participants in the extended Internet intervention condition will display significantly improved drinking outcomes at six months compared to participants in the minimal Internet intervention condition.**Secondary Hypothesis 2**: Participants in the extended Internet intervention condition will display significantly improved drinking outcomes at two years compared to participants in the minimal Internet intervention condition.**Secondary Hypothesis 3**: Participants in the extended Internet intervention conditions will display significantly improved health-related quality of life at twelve months compared to participants in the minimal Internet intervention condition.**Secondary Hypothesis 4**: Participants in the extended Internet intervention condition who have more involvement with the AHC intervention between baseline and twelve-month follow-up will demonstrate more improvement in drinking outcomes at twelve-month follow-up, compared to respondents in the extended Internet intervention condition who have less involvement with the AHC intervention.

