#### Secondary outcome measure

Secondary outcome measures are: (1) number of drinks in a typical week [39-41]; and (2) highest number of drinks on a single occasion. Finally, Health related Quality of Live (HRQOL) will be measured at each time point using the WHOQoL-8. This short form has been used in a number of countries, is robust psychometrically, and overall performance is strongly correlated with scores from the original WHOQoL [42].

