#### Secondary analyses

To test the difference across time between the two conditions (minimal or extended Internet-based intervention), a group (1, 2) x time (0, 6, 12, and 24) repeated measures MANOVA will be performed, including the primary outcome variable (AUDIT-C) and the two secondary outcome drinking variables (number of drinks in a typical week and greatest number of drinks on one occasion). Missing data will be replaced using a maximum likelihood approach. Planned contrasts will determine the nature of the differences observed. These planned contrasts will be stepped such that significant differences must be observed at the six months’ time point before comparisons will be made between condition at the twelve months’ time point, etc. Effect sizes will be calculated to determine the magnitude of differences in standard units. Interaction terms will be added to the MANOVA to test for sex differences (i.e., is there an interaction effect of subjects’ sex by experimental condition on drinking outcomes?). Finally, a separate repeated-measure ANOVA will be employed to test the hypothesis on the impact of receiving access to the Internet-based interventions on Health Related Quality of Life (secondary hypothesis 3). As part of these secondary analyses, we will also conduct a chi-square test to explore whether there is differential loss to follow-up between experimental conditions.

The proportion of each group that has sought further treatment (total and categorized into type of treatment such as support groups, residential, individual counseling) will be compared using χ^2^ statistics. If the proportion of treatment-seekers is high then further analyses will be conducted to explore the significance of this treatment to outcome.

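### Secondary Hypothesis 3 is about quality of life at twelve months, but the repeated-measures ANOVA assigned to it names no twelve-month contrast and, on its natural four-wave reading, does not isolate that time point

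*Protocol article*

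**What the plan says.** In the protocol article, under Hypotheses, Secondary Hypothesis 3 states that participants in the extended arm "will display significantly improved health-related quality of life at twelve months" relative to the minimal arm. That is one outcome at one time point. Under Secondary outcome measure, quality of life "will be measured at each time point using the WHOQoL-8".

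Under Secondary analyses, the test is tied to this hypothesis by its number: "a separate repeated-measure ANOVA will be employed to test the hypothesis on the impact of receiving access to the Internet-based interventions" on quality of life. The sentence lists no waves and no contrast.

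The same paragraph opens with the drinking model: "a group (1, 2) x time (0, 6, 12, and 24) repeated measures MANOVA will be performed". Its outcomes are AUDIT-C and the other two drinking measures; quality of life is not among them. The planned contrasts are described next and are stepped, so that "significant differences must be observed at the six months’ time point before comparisons will be made between condition at the twelve months’ time point". The quality-of-life ANOVA is introduced only after that, as a separate analysis.

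The primary hypothesis is also fixed at twelve months. The section on primary hypothesis testing gives it a dedicated analysis of covariance at twelve months, with the baseline value as covariate.

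**The concern.** A repeated-measures ANOVA over baseline, 6, 12 and 24 months offers two tests of treatment. The group main effect is the arm difference averaged over all four waves, including the wave before randomisation, where no effect can exist. The group-by-time term, with 3 degrees of freedom, asks whether the arm difference varies at all across waves. Neither is the arm difference at twelve months.

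Two things are at stake. Secondary Hypothesis 3 could be declared supported by a difference that exists only at another wave. The protocol's own background makes one such pattern plausible, since it argues that early changes in drinking are often not sustained; quality of life could likewise improve at six months and fade by twelve. In addition, because the text does not say which term decides the hypothesis, that choice stays open, and the two terms can behave very differently on the same data.

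**Working it through.** **Step 1: the plan's own sample size.** Inputs from Power analysis: AUDIT-C difference 1, SD 3.0, alpha 0.05, power 80%. The normal approximation, two-sided, gives 2 × (1.960 + 0.842)² × 3² / 1² = 141.3, so 142 per arm. The exact t-test gives 142.25, rounded up to 143 per arm, or 286, which is the plan's figure. Then 286 / 0.60 = 477, close to the 480 to be recruited. Expected numbers are 480 × 0.80 = 384 at twelve months and 480 × 0.60 = 288 at two years.

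**Step 2: inputs for the quality-of-life test.** The documents give no effect size, SD or correlation for WHOQoL-8. Assumptions: effect 1 / 3.0 = 0.333 SD, borrowed from AUDIT-C; equal correlation ρ between waves, from 0.4 to 0.7; complete data on N = 288 (n = 144 per arm) or N = 384 (n = 192 per arm).

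**Step 3: formulas.** Let d be the arm differences in SD units at 0, 6, 12 and 24 months, and d̄ their mean. Each test is at 0.05, with power from the noncentral F distribution.

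- Group by time: λ = (n/2) × Σ(d − d̄)² / (1 − ρ), with 3 and 3(2n − 2) df.
- Group main effect: λ = (n/2) × d̄² / [(1 + 3ρ)/4], with 1 and 2n − 2 df.
- Twelve-month ANCOVA: λ = (n/2) × d₁₂² / (1 − ρ²), with 1 and 2n − 3 df.

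**Step 4: effect at six months only, d = (0, 0.333, 0, 0).** Secondary Hypothesis 3 is false here. Σ(d − d̄)² = 0.1111 × 0.75 = 0.0833. For n = 144 and ρ = 0.4, λ = 72 × 0.0833 / 0.6 = 10.0. For n = 192 and ρ = 0.7, λ = 96 × 0.0833 / 0.3 = 26.7.

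| ρ | Interaction significant, N = 288 | Interaction significant, N = 384 | Twelve-month ANCOVA |
|---|---|---|---|
| 0.4 | 0.76 | 0.88 | 0.05 |
| 0.5 | 0.84 | 0.93 | 0.05 |
| 0.6 | 0.92 | 0.975 | 0.05 |
| 0.7 | 0.97 | 0.996 | 0.05 |

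A simulation with 143 per arm and 2,500 runs per case agrees: 77%, 84%, 92% and 98% for the interaction as ρ rises from 0.4 to 0.7, and 5% to 6% for the ANCOVA.

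**Step 5: effect at twelve months only, d = (0, 0, 0.333, 0), ρ = 0.5.** Secondary Hypothesis 3 is true here. For n = 192:

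- interaction λ = 96 × 0.0833 / 0.5 = 16.0;
- main effect λ = 96 × 0.0833² / 0.625 = 1.07;
- ANCOVA λ = 96 × 0.1111 / 0.75 = 14.2.

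| N | Interaction | Main effect | Twelve-month ANCOVA |
|---|---|---|---|
| 384 | 0.93 | 0.18 | 0.96 |
| 288 | 0.84 | 0.145 | 0.90 |

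**Step 6: the alternative reading.** If the ANOVA uses baseline and twelve months only, its group-by-time term is the twelve-month difference in change. With no twelve-month effect and effects at 6 and 24 months, the simulation rejects in 4.5% of runs (ρ = 0.5, 143 per arm).

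**The case against.** The strongest objection is that the article never says which waves enter the quality-of-life ANOVA. The list of four time points belongs to the drinking model, and collecting WHOQoL-8 at each wave does not settle which waves are analysed. Since the ANOVA is said to test a hypothesis defined at twelve months, a baseline and twelve-month ANOVA is compatible with the text and would be sound. This stands as a limit: the four-wave design is an inference from context, and a reader should not take it as stated.

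It can also be said that a condensed article may leave the contrast to an analysis plan. That carries less weight, because the article does name a test for this hypothesis by number, and gives a twelve-month ANCOVA to the primary hypothesis, which has the same form.

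The stepped contrasts might be thought to supply the twelve-month comparison. They are described for the drinking model before the separate ANOVA appears. If they were meant to apply, twelve months would be tested only after significance at six, a condition the hypothesis does not contain.

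Two stronger inferences are tempting and are not supported. One is that the plan would usually miss a real twelve-month effect. The interaction loses little (Step 5), and for an effect sustained equally at all follow-ups, with N = 384 and ρ = 0.5, it has power 0.93 and the main effect 0.87. The loss is serious for the main effect when the effect is confined to twelve months, and moderate for the interaction when half the effect is also present at 6 and 24 months (0.79 at N = 384, against 0.96 for ANCOVA). The other is to quote the 98% that arises when effects at 6 and 24 months surround none at twelve, with N = 384. That on-off-on pattern is unlikely, and 384 is the twelve-month number; 288 are expected at two years, where the figure is 0.93. The fading pattern in Step 4 is the fairer illustration.

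**Conclusion.** The concern holds in a limited form. The hypothesis and the test assigned to it do not match as written: one is fixed at twelve months, the other names no twelve-month contrast. Under the natural four-wave reading, the main exposure is a false claim of support. An effect that has vanished by twelve months would make the interaction significant in roughly three quarters to nearly all trials, against one in twenty for a test at twelve months. The exact percentages depend on the assumed 0.333 SD effect, equal correlations and complete data. That neither omnibus term isolates twelve months does not depend on those values. The text does not establish the four-wave reading, and the problem disappears if only baseline and twelve months are used. One secondary hypothesis is affected, the only one on quality of life; the primary analysis and the sample size stand.

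**What to change.** State that Secondary Hypothesis 3 is decided by the between-arm difference in WHOQoL-8 at twelve months adjusted for baseline. Either the ANCOVA form already used for the primary hypothesis or the month-12 contrast of a repeated-measures model will do. Say that this comparison does not depend on a significant six-month result. Keep the all-wave ANOVA as supportive, and list the waves it uses. The cost is a sentence or two of analysis wording, with no new data and no change to the sample size.

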## Discussion

The efficacy of IBIs to reduce drinking over short intervals has received increasing empirical evidence as is indicated in several systematic reviews [13-17]. However, research demonstrating that short-term changes in alcohol consumption are often not maintained [19,20] warrants an investigation of the efficacy of IBIs in long-term reductions in alcohol consumption. This project will be one of the first such trial to investigate the long-term benefits of IBIs among problem drinkers and compare the effectiveness of a normative personalized feedback intervention to one that contains a range of cognitive-behavioural and relapse prevention tools.
